#### Rehabilitation interventions

2.2.2

Following baseline assessment, patients will be randomized (1:1:1) to one of three intervention arms; all the interventions will be carried out with patients at their own homes, and will last 6 weeks:Tele-operated robot-mediated intervention: patients will undergo a remotely delivered cognitive stimulation program, via the tele-operated robot RoboXcare (SCAI SOLUTION Group S.p.A). Sessions will be led by a qualified neuropsychologist three times per week; each will last around 45 min, and will be scheduled to integrate into the patient’s daily routine. The intervention will employ previously validated cognitive stimulation protocols (Realdon et al., 2016; Rossetto et al., 2023) designed to target multiple domains, including attention, reasoning, executive functions, and visual-spatial skills, alongside procedural, semantic, and autobiographical memory. To ensure progressive stimulation, the difficulty level of these activities will be increased at fixed weekly intervals.Conversational robot-mediated intervention: patients will engage in personalized verbal and non-verbal interactions with the humanoid robot Pepper (SoftBank Robotics), connected to the CAIR (Culture-Aware AI and Robotics) system, a cloud-based architecture for diversity-aware and situated human–robot interaction previously presented and progressively extended in prior work (Grassi, 2024; Grassi et al., 2025). This cloud-based system supports tailored dialogues through a dedicated knowledge base and enables the integration of participant-specific information, including cultural background, language preferences, individual interests, and social relationships, entered via a tablet interface. The robotic system will be programmed to proactively initiate social interactions at least three times per week, to promote social engagement and reduce social withdrawal. Patients will also be allowed to initiate unlimited additional sessions independently; the frequency and duration of all interactions will be automatically recorded. To support sustained engagement, the CAIR server will systematically track interaction metrics and use them to adapt future conversations according to the topics and interaction patterns associated with higher individual engagement.Human-based intervention: patients will undergo a structured occupational therapy program focused on the prevention and management of behavioral and psychological symptoms of dementia (BPSD). This intervention will be delivered by a qualified occupational therapist in accordance with the Essential Levels of Assistance (Ministero della Salute, DPCM, 2017) and will include specialized caregiver training alongside home environment adaptation. The program will provide eight home-based sessions and two telephone-based sessions, specifically designed to enhance the quality of life and reduce the psychological burden for both the participant and their study partner. These personalized activities are tailored to the patient’s functional abilities and domestic context to promote social participation and emotional wellbeing.

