### Trial design

2.3

The study is designed as a single-blind, randomized controlled trial (RCT). Patients with neurocognitive disorders (both minor - i.e., MCI - and major, i.e., dementia), and presenting either MBI or BPSD, will be recruited from the Complex Units of Neurology and Geriatrics of the Azienda Ospedaliero-Universitaria di Modena (Modena), as well as from the Neurorehabilitation Units of the IRCCS Fondazione Don Carlo Gnocchi (Milan). After recruitment, individuals will be randomly assigned to one of two experimental groups involving robotic interventions (i.e., Telepresence robot or Pepper Robot) or to the active control group. Both the robotic and occupational therapy interventions will be conducted over 6 weeks. Primary and secondary outcome measures will be collected at baseline (T0), immediately post-intervention (T1, 6 weeks), and at follow-up (T2, 5 weeks after the end of the intervention, i.e., 11 weeks total time). The trial work plan is illustrated in Figure 1.

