### Primary outcome measures

3.1

The primary objective of this study is assessing the clinical and behavioral effects of home-based robot interventions compared to standard occupational therapy.

The primary endpoints of the study are defined as follows:Clinical improvement of apathy in patients, assessed using:Apathy Evaluation Scale (AES)Yoni-48 TaskEdinburgh Social Cognition Test (ESCoT)International Affective Picture System (IAPS)Interaction metrics with robotic systems, including:Response times of system componentsNumber and type of conversation topics addressed, and number of characters in each sentence, spoken per topic (e.g., sports, cinema, cooking, travel)Tone of verbal responses (neutral, humorous, aggressive, etc.)Attitude toward discussion topics (positive, negative, neutral)Objects recognized in the environment, along with labels that classify the identified items and their spatial relationships—for example, a lamp or a vase placed on a table.Number of verbal interactions per minute with the robotNumber of physical interactions per minute (e.g., hand, head, tablet, or base contact with the robot).

These interaction metrics, namely, the frequency and spontaneity of verbal and physical engagement with the Pepper robot, will also be interpreted as clinical indicators of the patient’s willingness to engage, given that reduced initiation and engagement are core features of apathy.3.Sensor-derived and kinematic measures during social grasping tasks, collected via BMR4RAPHAEL wearable sensors and cameras:Integral of the acceleration vector (m/s^2^)Peak velocity amplitude (m/s) and timingExecution time, reaction time, and deceleration (absolute and relative)Maximum hand excursion (degrees) and timingAsymmetry and kurtosis of movement.

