### Sample size calculation

3.5

To the best of our knowledge, robust evidence on the effect size of robot-mediated interventions primarily aimed at usability and behavioral outcomes in individuals with neurocognitive disorders is currently lacking. Therefore, a formal sample size calculation based on statistical power is not feasible. The proposed sample size is determined according to a pragmatic approach, taking into account the epidemiology of apathy within the target population and previous studies in the field of robotic interventions and dementia, which typically include small sample sizes (often fewer than 20 patients per arm; Hung et al., 2021; Mancioppi et al., 2019; Moyle et al., 2019).

In line with these considerations, the study aims to enroll approximately 25 patients per arm who will complete the trial. Accounting for an expected attrition rate of approximately 6%, the total sample to be randomized was set at 80 patients, allocated with a 1:1:1 ratio directly at enrollment (exact allocation per arm may vary slightly depending on block randomization, approximately 27, 27, and 26 patients per arm, given block randomization). The primary analysis will be conducted on an intention-to-treat basis, including all randomized participants; a per-protocol analysis restricted to patients who complete the trial will be reported as a secondary analysis.

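### The Pepper interaction metrics are read as frequency and spontaneity of engagement, but as listed none of them isolates contact that the patient starts

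*Protocol article*

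**What the plan says.** Section 3.1 (Primary outcome measures) lists interaction metrics with the robotic systems as one group of primary endpoints. The items are response times of system components, topics and sentence lengths, tone, attitude to topics, objects recognised in the room, and the numbers of verbal and of physical interactions, each per minute. The text that follows gives these metrics a clinical meaning: "namely, the frequency and spontaneity of verbal and physical engagement with the Pepper robot, will also be interpreted as clinical indicators". What they are taken to indicate is how willing the patient is to take part. The reason offered is short: "given that reduced initiation and engagement are core features of apathy".

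Section 2.2.2 (Rehabilitation interventions) describes two sources of contact in the Pepper arm. The robot is "programmed to proactively initiate social interactions at least three times per week". In addition, "Patients will also be allowed to initiate unlimited additional sessions independently". On logging, it says that "the frequency and duration of all interactions will be automatically recorded"; it does not say that the log records who started an interaction. The server will also track engagement and "use them to adapt future conversations according to the topics and interaction patterns associated with higher individual engagement". Section 2.3 (Trial design) sets the duration: "Both the robotic and occupational therapy interventions will be conducted over 6 weeks".

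**The concern.** The interpretation names spontaneity and appeals to initiation. To carry that meaning, a metric has to separate what the patient starts from what the robot starts. In this arm the two coexist by design, and the robot's share is fixed from below whatever the patient's initiative.

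The two items that count verbal and physical engagement are rates with no initiator attached. The remaining items describe machine latency, content, tone, attitude and surroundings, and they do not record the initiator either. Session frequency is logged under section 2.2.2 but does not appear in the endpoint list of section 3.1.

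What is at stake is the meaning of the result. A patient who only answers the robot's approaches and a patient who seeks the robot out could receive the same value, and that value would be read as evidence on initiation. The Discussion and section 4.1 (Anticipated results) expect these metrics to yield digital markers of behavioural change and treatment response, so the misreading would carry over to them.

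**Working it through.** The plan gives no figure for this point beyond the contact schedule, so the check works from that schedule and from the definition of the rate.

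**Inputs from the protocol article**
- Robot-started contacts: at least 3 per week (section 2.2.2), with no stated upper limit.
- Patient-started sessions: unlimited (section 2.2.2).
- Duration: 6 weeks (section 2.3).
- Denominator of the per-minute counts: not stated (section 3.1).

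**Assumed for illustration, not in the document**
- 10-minute sessions.
- 4 verbal interactions per minute, varied below for patient-started sessions.

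**Step 1. Contact that does not depend on the patient's initiative.** 3 × 6 = 18 robot-started contacts at the stated minimum.

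**Step 2. The minute is a session minute.** With s patient-started sessions per week:

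rate = [18 × 10 × r(robot) + 6s × 10 × r(patient)] / [(18 + 6s) × 10]

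If r(robot) = r(patient) = r, the rate reduces to r for every s. This is algebra and does not depend on the assumed 10 and 4. The calendar-minute column anticipates step 4.

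| s per week | Patient-started, 6 weeks | Share patient-started | Rate per session minute | Rate per calendar minute |
|---|---|---|---|---|
| 0 | 0 | 0% | 4.0 | 0.0119 |
| 1 | 6 | 25% | 4.0 | 0.0159 |
| 3 | 18 | 50% | 4.0 | 0.0238 |
| 7 | 42 | 70% | 4.0 | 0.0397 |
| 14 | 84 | 82% | 4.0 | 0.0675 |

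**Step 3. Session minute, unequal density.** Keep 4 per minute in robot-started sessions and take s = 14.
- 5 per minute in patient-started sessions: (180 × 4 + 840 × 5) / 1020 = 4.82.
- 3 per minute in patient-started sessions: (180 × 4 + 840 × 3) / 1020 = 3.18.

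The rate now moves, but its direction is set by how dense the contact is within sessions. The same 84 patient-started sessions can raise or lower it.

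**Step 4. The minute is a calendar minute.** Six weeks are 42 × 24 × 60 = 60,480 minutes.
- s = 0: 18 × 40 / 60,480 = 0.0119.
- s = 14: 102 × 40 / 60,480 = 0.0675, so the rate rises with use.
- s = 3 with 3 robot starts per week: 36 × 40 / 60,480 = 0.0238.
- s = 0 with 6 robot starts per week, which the schedule allows: 36 × 40 / 60,480 = 0.0238.

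The last two patients differ completely in initiative and score the same.

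**Step 5. What separates these patients.** A count or share by initiator does: 0, 6, 18, 42 and 84 sessions, or 0% to 82%, across the rows of the table.

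**The case against.** The strongest reply is that the stated rationale names engagement as well as initiation, and that the construct is willingness to engage. Speech and touch during contact bear directly on engagement. This stands: the mismatch concerns the spontaneity and initiation part of the reading only.

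Second, a reader might infer that the listed metrics cannot register initiation at all, or that a passive and an active patient must score the same. The documents do not support that. A touch on the robot's hand or an unprompted remark may be spontaneous within a session. The equality in step 2 needs a session-minute denominator and equal density, neither of which the article states. Under a calendar minute, heavier use does raise the rate.

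Third, that robot-started and patient-started contacts will be pooled is inferred from the absence of any split, and the list of metrics is introduced as inclusive, not closed. A condensed article may leave computation to the full protocol. This limits the point but does not remove it: the interpretive sentence refers back to the metrics just listed, and none of them carries the initiator.

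Fourth, a reader might infer that patient-started sessions can already be read from the log. Section 2.2.2 promises only the frequency and duration of all interactions. Study partners are also instructed on device operation, so a session that the robot did not start is not necessarily the patient's.

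Finally, apathy itself is measured by the Apathy Evaluation Scale, and section 3.4 (Statistical analysis) relates device metrics to outcomes through correlation and regression. That limits the consequence to the meaning of this metric group and of the markers built on it.

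**Conclusion.** The point holds in a limited form. As listed, the metrics do not isolate patient initiation under either reading of the per-minute denominator, yet section 3.1 reads spontaneity from them and justifies this partly by initiation. At least 18 robot-started contacts per patient arise regardless of the patient's initiative. Under a session minute with equal density, 0 and 84 patient-started sessions give the same rate; under a calendar minute, robot and patient starts are interchangeable.

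The invariance at equal density is algebraic. The specific rates rest on the assumed session length and densities, and pooling is inferred from the lack of a split. The rates remain usable as measures of engagement during contact, with one caution: because the system adapts conversations towards higher engagement, in-session density may partly reflect that tailoring. The comparison of arms on the Apathy Evaluation Scale is unaffected. This should be corrected, because it misstates what a primary endpoint group can show and is cheap to put right.

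**What to change.** 1. Record in the automatic log who started each session: robot, patient or study partner.
2. Add two items to the interaction metrics in section 3.1: patient-started sessions per week, and the share of robot-started contacts that the patient answers.
3. Tie the spontaneity and initiation interpretation to these two items only.
4. State the denominator of the per-minute rates and keep them as measures of in-session engagement.

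The cost is a start-source flag and one or two more reported metrics, with no new assessment. The flag should be in place before data collection, because the initiator may not be recoverable afterwards. If the initiator cannot be logged, drop the spontaneity and initiation interpretation from section 3.1 and keep only the engagement reading.

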### Secondary outcome measures

3.2

Secondary objectives are to evaluate the acceptability and feasibility of home-based robot-assisted interventions in individuals with cognitive or behavioral impairment exhibiting apathy, as well as the impact on caregiver burden and quality of life.

Secondary endpoints include:Participant and caregiver completion of the System Usability Scale (SUS; Brooke, 1996) to assess perceived usability of the robotic devices;Participant and caregiver responses on the Technology Acceptance Model (TAM; Venkatesh and Bala, 2008) questionnaire, evaluating perceived usefulness, ease of use, and overall acceptance of the technology.Caregiver outcomes, including stress levels and quality of life, assessed using:Neuropsychiatric Inventory (NPI)Zarit Burden Inventory (ZBI)Quality of Life in Alzheimer’s Disease (QoL-AD).

### Data collection

3.3

All study data will be pseudonymized to protect participant privacy. Original, identifiable data will be securely stored by each participating center in compliance with current Italian law on the protection and processing of personal and sensitive data, and the EU General Data Protection Regulation (GDPR 2016/679).

To maintain methodological rigor, a single blinded neuropsychologist will conduct all primary and secondary outcome evaluations for each participant throughout the study (T0, T1, and T2). Clinical, behavioral, and caregiver-reported data, as well as device-derived and sensor-based measurements, will be collected according to standardized procedures at each data collection point (T0, T1, T2).

We are committed to the highest standards of data integrity; all clinical, functional, and neurocognitive data will be collected by specialists and housed in a secure, dedicated dataset. Furthermore, the storage and processing of all research data will be performed in full compliance with established best practices and only after obtaining informed consent from each participant. All data will be entered in digital format, with quality control checks performed to ensure accuracy, completeness, and consistency across centers. Each recruiting center, as the autonomous data manager for the data collected at its site or through its devices, will have access to pseudonymized datasets stored on the REDCap platform at Fondazione Don Carlo Gnocchi of Milan, in accordance with the shared study protocol. Patients’ unique identification codes will be used consistently across all data collection points (T0, T1, T2) to ensure anonymity while allowing longitudinal tracking of outcomes.

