### Experimental procedure

2.2

Each participant will be assigned a unique identification code at the beginning of the study to ensure anonymity. The study follows a structured sequence of baseline assessment (T0), intervention, post-intervention assessment (T1), and follow-up (T2), as illustrated in Figure 1. All outcome assessments will be conducted by blinded evaluators, who will remain unaware of the patients’ group allocation.

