#### Assessment

2.2.1

At baseline (T0), post-intervention (T1, 6 weeks after T0), and follow-up assessment (T2, 5 weeks after T1), patients and their study partners will complete a comprehensive set of clinical, cognitive, behavioral, and psychosocial assessments, including:Neuropsychiatric Inventory (NPI; Cummings et al., 1994; Italian version by Binetti et al., 1998): assessment of non-cognitive behavioral disturbances in dementia across multiple domains, including frequency, severity, and caregiver distress.Apathy Evaluation Scale (AES; Marin et al., 1991; Italian version by Borgi et al., 2016): measurement of apathy in behavioral, cognitive, and emotional domains.Yoni-48 Task (Italian version by Isernia et al., 2022b; Isernia et al., 2023): computerized evaluation of first- and second-order affective and cognitive Theory of Mind (ToM).Edinburgh Social Cognition Test (ESCoT; Italian version by Isernia et al., 2022a): assessment of cognitive and affective ToM and understanding of interpersonal and intrapersonal social norms.International Affective Picture System (IAPS; Lang et al., 1997) with Self-Assessment Manikin (SAM; Bradley and Lang, 1994): evaluation of emotional valence and physiological arousal.Zarit Burden Inventory (Zarit et al., 1980; Italian version by Chattat et al., 2011): caregiver burden assessment.Quality of Life in Alzheimer’s Disease (QoL-AD; Logsdon et al., 1999; Italian version by Bianchetti et al., 2017): multidimensional quality-of-life assessment combining patient and caregiver ratings.Cognitive Reserve Index Questionnaire (CRIq; Italian version by Nucci et al., 2012): evaluation of cognitive reserve across education, occupational, and leisure activities.Cognitive assessments, including the Montreal Cognitive Assessment (MoCA; Nasreddine et al., 2005; Italian version by Santangelo et al., 2015).

The usability and the perceived usefulness, ease of use, and overall acceptance of the robotic systems will be subjectively evaluated at T1 using the System Usability Scale (SUS) and the Technology Acceptance Model (TAM).

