### Randomization and blinding

2.4

Eligible patients will be randomized using the “blockrand” package in (version 4.1.2; R Core Team, 2021). Randomization will be performed separately for each recruitment center and, within each center, will be stratified according to clinical and demographics variables, including diagnosis, sex, age, years of education, MOntreal Cognitive Assessment (MOCA) score, and apathy severity as measured by the Neuropsychiatric Inventory (NPI) apathy subscale. The allocation sequence will be prepared by a researcher not involved in either treatment delivery or outcome assessments. Investigators responsible for treatment administration and evaluations will not have access to the randomization list. Once generated, the list will be uploaded to REDCap in a non-visible format. Upon the creation of each new patient record and study ID, REDCap will automatically assign patients to their study group according to the predefined allocation sequence. In addition, different user access levels within REDCap will ensure that group allocation remains concealed from outcome assessors.

Patients will be randomly assigned to one of the two experimental groups or to the active control group (1:1:1 ratio).

Given the nature of the interventions, blinding will not be feasible for recruiting clinicians, researchers administering the interventions, or patients. However, outcome assessments at baseline (T0), post-intervention (T1), and follow-up (T2), including clinical endpoints and clinical/psychological questionnaires, will be conducted by trained evaluators who are blinded to group allocation. In addition, data analysts will remain blinded to treatment assignment throughout the analysis phase.

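### The blinded assessor is assigned every secondary outcome, including the robot usability and acceptance forms at T1, so the rule as written reveals robot versus occupational therapy before T2

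*Protocol article*

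**What the plan says.** All references are to the protocol article.

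- **Data collection (3.3):** "a single blinded neuropsychologist will conduct all primary and secondary outcome evaluations for each participant throughout the study (T0, T1, and T2"). No outcome is exempted.
- **Secondary outcome measures (3.2):** the endpoints include "Participant and caregiver completion of the System Usability Scale", aimed at the usability of the robotic devices, and participant and caregiver answers to the TAM, aimed at acceptance of the technology.
- **Assessment (2.2.1):** usability and acceptance of the robots "will be subjectively evaluated at T1 using the System Usability Scale (SUS) and the Technology Acceptance Model (TAM").
- **Rehabilitation interventions (2.2.2):** two arms receive a robot at home. The third receives occupational therapy from a human therapist.
- **Experimental procedure (2.2):** "All outcome assessments will be conducted by blinded evaluators, who will remain unaware of the patients’ group allocation".
- **Randomization and blinding (2.4):** the assessments at T0, T1 and T2, "including clinical endpoints and clinical/psychological questionnaires, will be conducted by trained evaluators who are blinded to group allocation". The same section says that "blinding will not be feasible for recruiting clinicians, researchers administering the interventions, or patients". For assessors it offers one safeguard, that "different user access levels within REDCap will ensure that group allocation remains concealed from outcome assessors".
- **Trial design (2.3):** T2 is five weeks after the end of the six-week intervention.

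**The concern.** A usability form about a robot can only be conducted with someone who had a robot. If the person who must stay blinded is also the person who conducts it, the task itself discloses the allocation. Its absence discloses the control arm equally well.

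Patients and treating staff know the allocation, and study partners of robot-arm patients are taught to use the device. The label single-blind therefore rests on the assessors. The contrast disclosed, robot against occupational therapy, is the one named in the primary objective (Primary outcome measures, 3.1). T2 is one of the two post-baseline time points in the planned Group by Time repeated-measures ANOVA (Statistical analysis, 3.4), so scores given by an assessor who knows the arm would enter the main analysis. Blinded analysts cannot undo a bias that is already in the recorded scores.

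**Working it through.** The point is a conflict between statements, so the main check is to read them together. The arithmetic only gives the number of participants concerned.

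**Step 1. Does the assessor's remit include SUS and TAM?** Section 3.3 covers every primary and secondary outcome at T0, T1 and T2. Section 3.2 lists SUS and TAM as secondary endpoints. They are therefore included, and no section exempts them or names another collector.

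**Step 2. Do the forms depend on the arm?** Sections 2.2.1 and 3.2 tie them to the robots. Section 2.2.2 gives a robot to two of three arms. Presence of the forms means a robot arm, and absence means occupational therapy.

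**Step 3. When does this happen?** SUS and TAM fall at T1 (6 weeks). T2 falls at 6 + 5 = 11 weeks. The assessor is the same for a given participant throughout, so the knowledge is carried to T2. Section 2.2.1 gives no order of instruments within T1, so disclosure before the other T1 scales can be neither asserted nor excluded.

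**Step 4. Is this compatible with the blinding statements?** Sections 2.2 and 2.4 have assessors unaware of allocation at all three visits. Steps 1 to 3 make that impossible at T2 if 3.3 is carried out literally. REDCap access levels can hide the allocation field. They cannot hide a form that the assessor conducts in person.

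**Step 5. How many participants?** Inputs from Sample size calculation (3.5): 25 completers per arm, about 6% attrition, 80 randomized.

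- Planned completers: 3 × 25 = 75.
- The plan's own total: 75 / (1 − 0.06) = 79.8, rounded up to 80. This reproduces the stated figure.
- Completers due SUS and TAM: 2 × 25 = 50, that is 50 / 75 = two thirds.
- Completers identified by the absence of the forms: 25.
- For comparison, as randomized (about 27, 27 and 26): 53 or 54 in robot arms and 26 or 27 in control.

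Anyone who attends T1 but is lost before T2 is disclosed too, but adds no T2 score. About 75 is therefore the relevant number for T2.

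**Step 6. Which outcomes are exposed?**

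| Outcome | Basis in the article | Exposure at T2 |
|---|---|---|
| AES, ESCoT, NPI | conducted by the assessor under 3.3 | main concern |
| Yoni-48 | described as computerized (2.2.1) | smaller |
| Grasping kinematics | sensor-derived (3.1) | smaller |
| Robot interaction metrics | for Pepper, frequency and duration logged automatically (2.2.2) | smaller |

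The article does not say how far AES ratings rest on the assessor's judgement, so its place in the first row is an assumption. No figure in the article allows the bias itself to be estimated.

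**The case against.** The strongest reply is that the sentence in 3.3 is loose shorthand. Taken literally, it would also have a neuropsychologist conduct the robot interaction metrics, which are listed as primary but come from the devices. Its evident purpose is one consistent rater per participant. SUS and TAM are described in terms of completion and responses, which suggests self-report. In 2.2.1 they stand in their own paragraph, outside the battery given at all three visits. Who hands over a self-report form is a detail that an article may leave to the full protocol.

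Much of this is plausible, and the authors may well intend separate collection. It does not remove the conflict. Section 3.3 states a specific rule without exception, and 2.4 expressly counts questionnaires among the blinded assessments. The point therefore rests on what the article states and not on detail it omits.

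Several stronger readings are tempting but not supported:

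- **All 80 patients are disclosed.** The plan expects attrition, and about 75 complete.
- **The assessor learns which robot.** Nothing says that the forms identify the device.
- **The interaction metrics disclose the arm too.** Nothing says that the assessor sees them. Device data are analysed at other universities (3.4).
- **The T1 comparison is certainly compromised.** That depends on an order of instruments that is not stated.
- **Assessor blinding is the only protection.** Section 2.4 also provides a hidden allocation list, automatic assignment and blinded analysts. These protect other steps of the trial and not the scoring at T2.

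**Conclusion.** The point holds in a limited form. As written, 3.3 contradicts 2.2 and 2.4. The assessor would learn robot versus occupational therapy for every participant seen at T1, about 50 and 25 of the 75 planned completers, before T2 is scored.

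This rests on two assumptions: that 3.3 is followed literally, and that SUS and TAM are not given to the control arm, which has no robot to rate. The consequence is a risk of detection bias, mainly for rater-dependent scales at T2. Neither its size nor its direction can be derived from the article. The wording needs correcting because scores collected unblinded cannot be re-blinded later, and because the correction is cheap.

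**What to change.** Amend 3.3 so that the blinded neuropsychologist conducts only the clinical, cognitive and grasping assessments at T0, T1 and T2. State that SUS and TAM are collected after the T1 battery is finished, either as a self-completed survey or by unblinded staff already in the trial, such as the occupational therapist who installs the device. Set REDCap rights so that the assessor cannot see those forms or whether they were filled in. Bring 2.2, 2.2.1, 2.4 and 3.2 into line with this.

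The cost is a change of wording, a change of user rights, and another collection route for two questionnaires. Recording the assessor's guess of the arm at T1 and T2 would show whether blinding held. That is optional, and its absence is not an error in the plan.
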